**Vercise DBS Dystonia Registry**

|  |                                                      |                     |
|--|------------------------------------------------------|---------------------|
|  | Target width of 1- $\alpha$ confidence interval (CI) | 0.30                |
|  | Probability of achieving target CI width             | 0.95                |
|  | Minimum subgroup prevalence                          | 0.25                |
|  | Attrition (%)                                        | 30                  |
|  | N (both subgroups)                            | 200 subjects |

## 4. Introduction

Dystonia is a neurological condition characterized by involuntary and sustained muscle spasms which can force affected parts of the body into abnormal movements or postures. Dystonia is an umbrella term covering a broad spectrum of conditions, which can be classified depending on the cause of dystonia, body areas or segments affected by dystonia, and time of onset of dystonia. Dystonia can be classified as primary or secondary depending on the cause of dystonia. Primary dystonia is idiopathic in nature whereas secondary dystonia also called as acquired dystonia results from apparent outside factors and can be attributed to a specific cause. Types of secondary dystonia include drug-induced (tardive) dystonia, dystonic cerebral palsy, dystonia resulting from Parkinson's disease (PD), metabolic disorders, or brain injury. Dystonia can be localized either to a single body region (focal), or can involve more than one body region. Depending on the continuity of body regions involved dystonia can be classified as multifocal, hemidystonia, or generalized. Types of focal dystonias include cervical dystonia, blepharospasm, oromandibular, or laryngeal or focal hand dystonia. Multifocal dystonia involves two or more of the listed focal dystonia. In generalized dystonia, the trunk and at least 2 other sites are involved, whereas hemidystonia affects the body and limbs on one side. Dystonia can also be characterized as early-onset or late-onset depending on the time of onset of dystonia symptoms. On average, the signs and symptoms of early-onset primary dystonia appear around age 12.

The magnitude of different conditions covered under dystonia makes it challenging to determine the accurate prevalence for dystonia. Based on minimum prevalence estimates, primary dystonia is believed to be the third most frequent movement disorder after essential tremor and Parkinson's disease (Defazio et al., 2010).

In the past, for subjects who had reduced response to pharmacotherapy, thalamotomy (lesioning areas of the thalamus), and pallidotomy (lesioning areas of the globus pallidus) were the only available options for treating dystonia. However these treatment options frequently produced side effects and are now considered less advantageous due to the introduction of reversible, adjustable methods such as deep brain stimulation (DBS), and transcranial neurostimulation (TNS). In the 1990s, high-frequency deep brain stimulation was demonstrated to be safe and effective in reducing the motor complications of subjects with Parkinson's disease (Limousin, et al. 1995). In 2003, FDA approved use of DBS for the treatment of primary dystonia. Since receiving approval, the safety and efficacy of DBS for PD (Deuschl et al., 2006; Follett et al., 2010; Fraix et al., 2006; Weaver et al., 2009; Okun et al., 2012; Schuepbach et al., 2013) and dystonia (Krause et al., 2004, Markun et al. 2012; Valdeoriola et al., 2007, Krause et al., 2004; Egidi et al., 2007; Borggraefe et al., 2012, Volkmann et al., 2012) has been substantiated by numerous observational case series and clinical trials. Studies using deep brain stimulation for dystonia focus on treatment of

multitude of dystonia conditions including primary generalized (Kupsh et al., 2006; Krause et al., 2004; Heueto et al., 2010), cervical dystonia (Kiss et al., 2007), tardive dystonia (Gruber et al., 2009), and other types of secondary dystonia (Krause et al., 2004; Pretto et al., 2008; Vidailhet et al., 2009; Egidi et al., 2007; Kim et al., 2011). All these studies show highly effective results with use of DBS for treatment of dystonia.

This study will document characteristics of real-world outcomes for Boston Scientific Corporation's commercially approved Vercise System for Deep Brain Stimulation (DBS), when used according to the applicable Directions for Use. The Vercise Deep Brain Stimulation System is indicated for use in unilateral or bilateral stimulation of the subthalamic nucleus (STN) and internal globus pallidus (GPi) for treatment of primary and secondary dystonia.

#### **4.1. *Precedence***

In 1997, the Medtronic Activa System received U.S. FDA approval for unilateral thalamic stimulation for the treatment of tremor (P960009). In 2002, it also received FDA approval (P960009/S007) for bilateral stimulation of the STN or GPi (globus pallidus interna) for the treatment of PD. Additionally, Medtronic Activa® DBS received CE Marking for the treatment of tremor in 1993, Parkinson's disease in 1998, primary dystonia in 2003, and obsessive compulsive disorder in 2009.

St. Jude Medical (ANS/St. Jude) began a U.S. study of their Libra DBS device for PD in 2005 and their results (136 subjects received bilateral stimulation of subthalamic nucleus) were published in Lancet Neurology (Okun, et al. 2012) in 2012. This device has not yet received FDA approval. St. Jude Medical received CE Marking for Parkinson's disease in 2009, and for intractable primary and secondary dystonia in April 2013.

Boston Scientific began a European study in 2010 to document subject outcomes, including effectiveness, safety, and health economic data of the Vercise™ Deep Brain Stimulation system, which is ongoing. The Vercise™ system received CE mark for treatment of Parkinson's disease in September 2012, intractable primary and secondary dystonia in September 2013 and Essential Tremor in July 2014.

#### **4.2. *Multicenter trials and Randomized clinical studies***

Given that DBS has been commercially available for more than a decade, a large number of clinical studies have been published on this therapy. Close to a hundred clinical studies have been performed in dystonia patients treated with DBS. Of these, a total of twenty-eight are multi-center and randomized clinical trials (RCTs). Efficacy data from three (Valdeoriola et al., 2007; Kiss et al., 2010; Volkmann et al., 2012) recent prospective, multicenter, randomized clinical trials are discussed here. Collectively these studies present data at follow-up durations between 3 months to 5 years. At most centers, the preferred DBS target for patients with dystonia has been the globus pallidus internus (GPi). However, stimulation of the STN has also been effective for controlling dystonic symptoms. A recent study (Schjerling et al., 2013) conducted a double-blind randomized study comparing the STN and the GPi as DBS targets in the treatment of dystonia, and is also discussed here.

Valdeoriola et al., 2007 assessed the tolerability and clinical effects of bilateral pallidal DBS on motor impairment, functional disability, quality of life, pain and mood in 24 patients with medically refractory primary generalized or segmental dystonia. Bilateral GPi DBS significantly improved dystonic symptoms with both open and blind assessments. Improvement of disability, pain and mood was also observed. Seventeen of the 22 patients who completed the study achieved a good or partial response to pallidal DBS. Mood showed a mild but significant improvement after surgery and a mean 40% improvement in the physical aspects of the health related Quality of life (HRQoL). No significant changes in social function and mental health were seen. In summary, this study showed significantly improved motor symptoms, pain, quality of life and mood after GPi DBS.

Kiss et al., 2010 performed a prospective, single-blind, multi-center study assessing the efficacy and safety of bilateral GPi-DBS in 10 patients with severe, chronic, medication-resistant cervical dystonia. Two blinded neurologists assessed patients before surgery and at 6 and 12 months post-operatively using the Toronto Western Spasmodic Torticollis Rating Scale (TWSTRS). At the follow-up duration of one year, the total TWSTRS improved by 59% as compared to baseline score. There were significant improvements in quality of life (24%) and depression scores (58%), minor effects on swallowing and cognitive tests.

---

 As found in PubMed database (available through National Center for Biotechnology Information [NCBI] at the National Library of Medicine [NLB] located at the National Institute of Health [NIH]). Search terms: "dystonia" AND "deep brain stimulation", Limits: Clinical trial, Comparative study, Controlled clinical trial, Multicenter clinical trial, Randomized clinical trial. Date searched: 15 July, 2014

 As found in PubMed database (available through National Center for Biotechnology Information [NCBI] at the National Library of Medicine [NLB] located at the National Institute of Health [NIH]). Search terms: "dystonia" AND "deep brain stimulation", Limits: Multicenter clinical trial, Randomized clinical trial. Date searched: 15 July, 2014

Medications were reduced after surgery and no further botulinum toxin injections performed. Complications were mild and reversible in four patients. Some changes in neuropsychological tests were observed, although these did not impact daily life or employment. In conclusion the authors supported the efficacy and safety of GPi-DBS for the treatment of patients with severe and prolonged cervical dystonia who have failed medical management.

Volkman et al., 2012 assessed safety and efficacy of GPi stimulation in patients with primary generalized or segmental dystonia prospectively followed up for 5 years in a controlled multicenter trial. Forty (40) patients were randomly assigned to either sham neurostimulation or neurostimulation of the internal globus pallidus for a period of 3 months and thereafter all patients completed 6 months of active neurostimulation. The primary endpoint was the change in dystonia severity at 3 years and 5 years as assessed by open-label ratings of the Burke-Fahn-Marsden dystonia rating scale (BFMDRS) motor score compared with the preoperative baseline and the 6-month visit. The primary endpoint was analyzed on an intent-to-treat basis. An intent-to-treat analysis including all patients from the parent trial showed significant improvements in dystonia severity at 3 years and 5 years compared with baseline, which corresponded 47.9% improvement at 6 months (n=40); 61.1% improvement at 3 years (n=31); 57.8% improvement at 5 years (n=32). 49 new adverse events occurred between 6 months and 5 years. Authors concluded sustained benefits and an acceptable safety profile for the treated dystonia population.

Schjerling et al., 2013 compared the subthalamic nucleus (STN) with the globus pallidus internus (GPi) as a stimulation target for deep brain stimulation (DBS) for medically refractory dystonia. In a prospective double-blind crossover study, electrodes were bilaterally implanted in the STN and GPi of 12 patients with focal, multifocal, or generalized dystonia. Each patient was randomly selected to undergo initial bilateral stimulation of either the STN or the GPi for 6 months, followed by bilateral stimulation of the other nucleus for another 6 months. Preoperative and postoperative ratings were assessed by using the Burke-Fahn-Marsden Dystonia Rating Scale (BFMDRS) and video recordings. Quality of life was evaluated by using questionnaires (36-item Short Form Health Survey). Supplemental Toronto Western Spasmodic Torticollis Rating Scale (TWSTRS) scores were assessed for patients with focal dystonia (torticollis) by examining the video recordings. On average for all patients, DBS significantly improved the BFMDRS movement scores ( $p < 0.05$ ) and quality of life physical scores ( $p < 0.01$ ). At 6 months, BFMDRS movement score with STN stimulation had a non-significant improvement of the TWSTRS movement score as compared to GPi stimulation. Quality of life did not differ significantly regardless of which nucleus was stimulated. The authors concluded that further studies are necessary before the optimal target can be concluded.

### **4.3. *Factors affecting DBS treatment in dystonia patients***

Improvement in DBS treatment for dystonia is variable from one patient to another, and could depend on factors related to the disease state or treatment. A number of studies have focused on understanding factors that could possibly have predictive value on the magnitude of improvement with DBS treatment for dystonia. These factors include dystonia etiology, and duration of disease. A recent study also showed higher volume of activation of GPi in highly improved patients compared to less improved patients.

As mentioned earlier, primary dystonia is idiopathic in nature, whereas secondary dystonia results from apparent outside factors and can be attributed to a specific cause. A group of early-onset primary dystonia syndromes can be classified based on clinical presentation and assigned to a DYT number. At present about 20 monogenetic dystonia syndromes, include seven primary dystonia syndromes (DYT1, 2, 4, 6, 7, 13, and 17) have been classified. Of these dystonia syndromes, the genes TOR1A (causing DYT1), and THAP (DYT6) have been identified. Primary dystonia patients, specifically with DYT1 positive mutation have been typically shown to have better outcomes as compared to secondary dystonia patients (Borggraefe et al., 2012, Egidi et al., 2007, Krause et al., 2004, Markun et al. 2007, Lumsden et al, 2013). Treatment outcome in secondary dystonia patients has been quite poor (Krause et al., 2004; Pretto et al., 2008; Vidailhet et al., 2009), with the exception of drug-induced secondary dystonia patients who seem to benefit significantly from DBS treatment (Egidi et al., 2007). Considering the variability in treatment effect, a subgroup analysis between primary and secondary dystonia patients will be performed. Further exploratory analysis in other primary monogenetic dystonia syndrome population is also intended.

A number of studies show that duration of disease in primary dystonia correlates with magnitude of improvement. Patients with shorter duration of the disease may benefit more than patients who have exhibited symptoms for a longer duration (Egidi et al., 2007; Markun,et al., 2007; Andrews et al., 2010; Isaias et al., 2011; Lumsden et al, 2013). Younger patients with short disease duration benefit more and faster than older patients (Isaias et al., 2011) Lumsden et al., 2013 recommends DBS implantation in early, preferably within 5 years of onset, are made to maximize benefits and reduce the childhood experience of dystonia. Based on this evidence, analysis on the effect of disease duration on DBS treatment will be performed.

In summary, the results from these recent multi-center, randomized controlled trials provide solid evidence in support of the effectiveness and safety of DBS as a therapy for PD. Further, studies analyzing the effect of the disease factors on treatment effect provide the basis for

need for subgroup analysis based on the disease factors of this population. This review is used as the basis for the design of this study.

## **5. Device Description**

The Boston Scientific Vercise™ DBS System received CE mark approval in September 2012 for treatment of Parkinson's disease, in September 2013 for treatment of intractable primary and secondary dystonia and in July 2014 for Essential Tremor.

The implantable portion of the Vercise™ System includes leads for bilateral stimulation and extensions that allow the leads to be extended to reach the Implantable Pulse Generator (IPG) near the clavicle. The electrode array is typically placed into the brain, targeting the subthalamic nucleus (STN) or Globus Pallidus (GPi). Leads can provide stimulation in a ring mode (around the lead) or if the directional lead is used in a directional mode (away from the lead). Once the leads are placed, they are typically secured using physician's standard lead fixation technique. A SureTek™ Burr Hole Cover may be used. Since the leads are often placed under the scalp for some time before being connected to lead extensions or IPG, lead boots will be provided to cover the proximal ends of the leads during this period.

Surgical tools for the Vercise™ System include a tunneler (similar to the commercially available Precision SCS tunneling tool). A lead stop (which may be attached to the lead to allow the lead to be located at the appropriate depth in the tissue during its initial placement) will also be provided.

External devices including a Clinician Programmer, Remote Control and, if needed, a charging system will also be provided for patient/physician use. A charging collar has been designed to facilitate the charging of the IPG in the sub-clavicular location.

The Pocket Adaptor allows the Vercise IPG to be used in subjects implanted with non-BSC leads.

## **6. Objectives**

To compile characteristics of real-world outcomes, economic value and technical performance of Boston Scientific Corporation's commercially approved Vercise™ DBS system, when used according to applicable Directions for Use (DFU)

## **7. Endpoints**

### Clinical Endpoints

All clinical endpoints will be analyzed separately for subjects with primary and secondary dystonia sub-groups. The Statistical Analysis Plan will provide details on whether descriptive statistics or statistical hypothesis testing will be performed for each endpoint. The specific assessment or questionnaire to be used depends on the

subjects' dystonia classification and age as detailed in Table 11-2. The following clinical endpoints will be analyzed for each sub-group of dystonia separately (Primary vs. Secondary):

- Proportion of subjects with 30% or greater reduction in Baseline BFMDRS or TWSTRS score at 26 weeks, 52 weeks, 2 years, and 3 years post first lead placement
- Change in BFMDRS scores from Baseline to 26 weeks, 52 weeks, 2 years, and 3 years post first lead placement
- Change in TWSTRS scores from Baseline to 26 weeks, 52 weeks, 2 years, and 3 years post first lead placement
- Change in SF-36v2 score (SF-10v2 in patients under the age of 18 years at the time of consent) from Baseline to 26 weeks, 52 weeks, 2 years, and 3 years post first lead placement
- Change in GDS scores from Baseline to 26 weeks, 52 weeks, 2 years, and 3 years post first lead placement.
- Clinical Global Impression of Change (CGI-C) rating score, as assessed by neurologist, at 26 weeks, 52 weeks, 2 years, and 3 years post first lead placement
- Clinical Global Impression of Change – Subject (CGI-C: Sub), as assessed by subject, at 26 weeks, 52 weeks, 2 years, and 3 years post first lead placement
- Clinical Global Impression of Change – Caregiver (CGI-C: Crg), as assessed by caregiver, at 26 weeks, 52 weeks, 2 years, and 3 years post first lead placement

#### Safety Parameters

Rates of occurrence of all serious adverse events (SAEs) and all adverse device effects (ADEs), including serious adverse device effects (SADEs) and unanticipated serious adverse device effects (USADEs) at 3 years post first lead placement

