|                           | 
Staged Implants: Device Placement
 
 
Day 0 is the date of the first lead implant procedure or IPG placement if the Pocket Adaptor is used.
 
Typically 1 to 3 procedures per site's preferred practice.
 
 
Activation
 
 
Programming/Device activation
 
 
Programming and Evaluation visits
 
 
Up to Week 12 visit (<math>\pm 21</math> days) (programming only)
 
Week 26 visit (<math>\pm 21</math> days)
 
Week 52 visit (<math>\pm 56</math> days)
 
Year 2 visit (<math>\pm 56</math> days)
 
 
End of Study visit: Programming and Evaluation visit
 
 
Year 3 visit (<math>\pm 56</math> days)
 
 
Subjects may come in as needed for programming and/or evaluation of adverse events during the study.
 |
| Study Duration     | The study will be considered complete after all subjects complete their year 3 visit                                                                                                                                                                                                                                                                                                                                                                                                                                                                                                                                                                                                                                                                                                                                                                                                                                                                                                   |

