| Satisfaction with Treatment (SWT)‡                          |           | X                                      |                                            |                                             |            |                                 | X                                | X                                | X                               | X                                |                                 |
| Short Form Health Survey-10 (SF-10v2)                       |           | X                                      | X #                             |                                             |            |                                 | X                                | X                                | X                               | X                                |                                 |
| Short Form Health Survey-36 (SF-36v2)                       |           | X                                      | X #                             |                                             |            |                                 | X                                | X                                | X                               | X                                |                                 |
| Toronto Western Spasmodic Torticollis Rating Scale (TWSTRS) |           | X                                      | X                                          |                                             |            |                                 | X                                | X                                | X                               | X                                |                                 |

\* Assessments and questionnaires should be utilized based on subject classification and age, and as highlighted in Table 11-2. Baseline Clinician administered assessments done as part of standard of care screening to determine eligibility for DBS up to 180 days prior to baseline may be used for this Baseline Visit (no repetition needed).

Pocket Adaptor (PA): Subjects receiving a pocket adaptor to connect non-BSC leads to BSC IPG

X = required; O = optional

† Only adverse events related to the device, stimulation, or procedure, and serious adverse events will be recorded

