### **11.6. *Implant Procedure(s) of Vercise System***

Detailed directions for use will be available to each investigator and investigational site in the form of instructional manuals and training by BSC staff. Because DBS is a well-established therapy, neurosurgeons, neurologists, and their staffs have developed their own best procedures and practices for implant, activation, and programming. Standard practices, per local DFUs will be followed for the placement of the Vercise system.

The date of the first lead placement will be considered as Day 0. Alternatively, for subjects receiving BSC IPG and BSC Pocket adaptor as a replacement to non-BSC IPG, the day of BSC IPG implant will be considered as Day 0. Also, if newly marked CE active components- such as the lead or IPG are used, then that day shall be considered as Day 0. All subsequent study schedule visits will occur based on the timing of the Day 0 visit.

Standard practices, per local DFUs will be followed for the placement of the Vercise system.

Post-operative imaging is recommended to be done within 3 months following placement of leads to confirm lead position. A computerized tomography (CT scan) with at least 1.25 mm slice thickness is recommended.

The implant procedure must be performed within 6 months of the baseline.

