#### **11.14.     *Study Completion***

De-novo subjects will be followed for 3 years after first lead implant, and subjects with Pocket Adaptor will be followed for 3 years post Vercise IPG placement. The study will be considered complete once all subjects have completed Year 3 Visit.

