## **12.2. General Statistical Methods**

### **12.2.1. Analysis Sets**

All clinical endpoints will be analyzed on both intent-to-treat and a per-protocol basis. Safety endpoints will be analyzed in the safety analysis set.

- **Intent-to-Treat (ITT)**

In the intent-to-treat analysis, all enrolled subjects who undergo a Vercise DBS implant procedure will be included in the analysis.

- **Per-Protocol**

In the per-protocol analysis, only subjects completing all scheduled protocol visits through 52 weeks with no major protocol deviations will be included in the analysis. A comprehensive list of major protocol deviations will be provided in the Statistical Analysis Plan.

- **Safety Analysis Set**

In the safety analysis, all subjects who sign the IRB/EC-approved written Informed Consent form will be included.

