## **14. Study Assessments**

### **14.1. *Adverse Events***

Adverse event evaluation will be conducted to identify adverse events occurring during the study and to classify them with regards to seriousness, severity, and relationship to either study procedure and/or study-device action. Additionally, an assessment of actions taken to address adverse events and their outcome will be conducted. Safety events will be reported as specified in Table 20-3. Only non-serious adverse events that are related to the device, stimulation, or procedure, and serious adverse events will be recorded. SAEs and USADEs will be collected from the time of informed consent through the end of the study.

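### The safety endpoint is timed from first lead placement, which conflicts with the protocol's own Day 0 for Pocket Adaptor subjects, and one pooled rate may understate the de novo rate

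*Protocol*

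**What the plan says.** The safety parameters in Section 7, repeated in the synopsis, are rates of all SAEs and all ADEs, including SADEs and "unanticipated serious adverse device effects (USADEs) at 3 years post first lead placement". Section 8.1 likewise runs each subject's follow-up for three years from first lead placement. Neither place makes an exception.

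The protocol also admits PA subjects. Section 5 says "The Pocket Adaptor allows the Vercise IPG to be used in subjects implanted with non-BSC leads", and the footnote to Table 11-1 describes them as "Subjects receiving a pocket adaptor to connect non-BSC leads to BSC IPG".

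For these subjects other parts of the protocol set a different clock:

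- Synopsis, study schedule: "Day 0 is the date of the first lead implant procedure or IPG placement if the Pocket Adaptor is used".
- Section 11.6: for replacement of a non-BSC IPG, "the day of BSC IPG implant will be considered as Day 0".
- Section 11.14: "subjects with Pocket Adaptor will be followed for 3 years post Vercise IPG placement".

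On collection, Section 14.1 states "SAEs and USADEs will be collected from the time of informed consent through the end of the study", and Section 20.4 starts ADE reporting at consent too. On the analysis population, Section 12.2.1 defines one safety set in which "all subjects who sign the IRB/EC-approved written Informed Consent form will be included". The six subgroups listed in Section 12.3.2 do not include PA versus de novo.

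**The concern.** A PA subject's first lead placement precedes consent, possibly by years. Read literally, the endpoint window for that subject opens before any event can be recorded. If the leads were placed more than three years before consent, it closes before collection begins. The authors wrote a PA exception into the visit schedule and the study-completion rule but did not carry it into the safety endpoint.

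Correcting the anchor leaves a second problem. Counted from Day 0, a de novo subject's window includes intracranial lead surgery, while a PA subject's window starts with a generator replacement. Sections 19.1 and 19.3 list hemorrhagic stroke, CSF leak, injury to the brain and poor initial lead location among many anticipated events. Poor initial lead location cannot newly arise where the leads are left untouched, and the others are tied largely to cranial surgery. One rate over both groups describes neither. At stake is how the registry's safety rate is read: a physician considering a new implant may take a pooled figure as the risk of that procedure.

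**Working it through.** **Step 1: the anchors side by side.**

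| Place in protocol | De novo subject | PA subject |
|---|---|---|
| Section 7 and synopsis, safety parameters | 3 years from first lead placement | the same wording, no exception |
| Section 8.1 | 3 years from first lead placement | the same wording, no exception |
| Synopsis schedule, Section 11.6 (Day 0) | first lead placement | Vercise IPG placement |
| Section 11.14 (end of follow-up) | 3 years from first lead implant | 3 years from Vercise IPG placement |
| Sections 14.1 and 20.4 (start of collection) | consent, before lead surgery | consent, after the original lead surgery |

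The first two rows agree with the next two for de novo subjects and contradict them for PA subjects.

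**Step 2: effect of pooling.** The protocol states no safety rate, PA share or risk by implant type, so there is no figure to reproduce. All inputs below are assumptions. Consented subjects who are never implanted are left out for simplicity.

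Let f be the PA share, r the 3-year de novo risk and r_P the 3-year PA risk. Write r_P = r(1 − q), where q is the shortfall in PA risk relative to de novo risk. Then

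pooled risk = (1 − f)r + f·r_P = r(1 − f·q),

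and the relative understatement of the de novo risk is f·q.

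*(a) Events confined to lead surgery.* Here r_P = 0, so q = 1 and the pooled proportion is r(1 − f). With r = 10%:

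| f | Pooled proportion |
|---|---|
| 5% | 0.10 × 0.95 = 9.5% |
| 10% | 0.10 × 0.90 = 9.0% |
| 20% | 0.10 × 0.80 = 8.0% |
| 30% | 0.10 × 0.70 = 7.0% |

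*(b) All SAEs and ADEs.* PA subjects still have IPG surgery, hardware and stimulation, so q is below 1. With r = 30% and q = 0.5:

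| f | f·q | Pooled rate |
|---|---|---|
| 5% | 2.5% | 0.30 × 0.975 = 29.25% |
| 10% | 5% | 0.30 × 0.95 = 28.5% |
| 20% | 10% | 0.30 × 0.90 = 27.0% |
| 30% | 15% | 0.30 × 0.85 = 25.5% |

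*(c) Equal or higher PA risk.* With q = 0 the pooled rate stays at 30% for every f. With q below 0 it rises: q = −0.5 and f = 20% give 0.30 × 1.10 = 33%.

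Both direction and size therefore depend on f and q. The protocol sets no cap on the PA share, so the design does not bound the effect.

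**The case against.** The strongest reply is that the PA clock is defined. The synopsis and Sections 11.6 and 11.14 leave no doubt when it starts and ends, and the same lead-placement phrase is attached to every timed clinical endpoint in Section 7, so it reads as loose wording for Day 0. This stands. A reader might infer that the endpoint cannot be computed for PA subjects. The documents do not support that: the observation window exists, and the endpoint text fails to use it.

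A reader might also infer that including PA subjects lowers the SAE and ADE rates. That too goes beyond the documents. SAEs are counted whatever their cause. Section 19.3 names device replacement as a source of risk. Infection, implant-site complications, hardware failure and stimulation effects apply to PA subjects as well. The r(1 − f) arithmetic covers only events that lead surgery alone can cause and must not be carried over to the overall rates.

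Two further points have force. The stated objective is real-world performance of the system in on-label use, which includes the adaptor, so an overall registry rate is legitimate. And the analysis plan, not shown here, may already split the safety tables. Neither removes the conflict over the anchor, because the protocol itself fixes the endpoint definition. They do mean that the split belongs beside an overall rate and need not replace it.

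On attribution, Table 20.2-1 defines ADEs, and hence SADEs and USADEs, by relation to the study device. Events from the retained leads therefore enter mainly through the all-cause SAE count.

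**Conclusion.** The concern holds in a limited form. The safety endpoint in Section 7 and the synopsis, and the follow-up statement in Section 8.1, contradict the protocol's own Day 0 and follow-up rules for PA subjects. This follows from the text and needs no assumption. The original lead surgery of these subjects is unobserved, so a single rate mixes two surgical exposures and may understate the de novo rate.

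The size is conditional. For all SAEs and ADEs the relative understatement is about 2.5% to 15% if f is 5% to 30% and q is 0.5. It is zero if PA subjects carry the same 3-year risk and reversed if they carry more. For events confined to lead surgery it equals f. No hypothesis test or safety sample size depends on the point. It is nonetheless worth correcting, because safety is a main output of the registry and the stated rule does not fit a group that the protocol deliberately admits.

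**What to change.** Restate the safety endpoint in Section 7 and the synopsis as rates through 3 years after Day 0, and align Section 8.1. Spell out the anchor in the endpoint itself: first lead placement for de novo subjects, Vercise IPG placement for PA subjects. This matters because Section 11.6 adds a further Day 0 clause, for newly CE-marked active components, that the synopsis does not carry.

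Report the rates separately for de novo and PA subjects, alongside any overall registry rate. In the PA table, identify events attributed to the retained non-BSC leads.

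The cost is some rewording and one split of the safety tables by a status that already determines Day 0 and the visit schedule. No new visits, data or subjects are needed. The downside is that the de novo rate rests on fewer subjects and may be somewhat higher: with 200 implanted and f = 5% to 30%, the de novo denominator is 200 × 0.95 = 190 down to 200 × 0.70 = 140.
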